### Data Tracking

Data will be tracked in Google Sheets, linked to each survey. This will also help identify participant’s responses with the date, time, and enrollment number. Study packet responses will be saved in a password-protected box. Retrospective review will also be done to ensure each enrollment number matches the correct medical record number. Our research team will have access to the final trial dataset, and we will keep the data for 5 years after the study is completed.

### Ethical Considerations

We obtained institutional review board (IRB) approval for this protocol (IRB 23-0385), and the parent study (the Hospitalist Project) is also IRB approved (IBR 16-1131). Written, informed consent to participate in the Hospitalist Project will be obtained from all participants. Participants will also verbally consent and be enrolled in the I-C-CKD study.

Patients will be informed that the study is completely voluntary and may withdraw at any time. Discontinuation will also occur if patients are in acute distress or experience declining health conditions during hospitalization. For example, if the patient is transferred to intensive care unit, is intubated, or has an altered mental status and can no longer participate, then we will withdraw them from the study. Patients will also be able to meet with patient educator who is a licensed clinical social worker if they are interested in additional information, are under distress, or want posttrial care.

Patients will receive US $25 gift cards upon completion of the pretest and posttest surveys and US $10 for partially completed surveys. All participants will be compensated. This study is minimal risk, as an education intervention is the only experimental procedure involved. Additionally, reports will be made to the IRB in the case of an adverse event, along with any protocol modifications to the investigators, IRB, trial participants, journals, and regulators.

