### Randomization

Participants will be randomly assigned using a computerized spreadsheet, assigning each participant a random number. Participants who are assigned an odd number will be assigned to the intervention group. Participants who are assigned an even number will be assigned to the control group. The RA will begin by identifying an eligible participant who consented to the Hospitalist Project. Then, they will use the randomization spreadsheet to determine if the participant will be part of the intervention group or the control group. They will then approach the patient with the appropriate form and study packet.

The RA will complete the randomization, assignment, and enrollment process.

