### Intervention Group

The RA will meet each participant and conduct the pretest survey in the participant’s private hospital room. The computerized adaptive education intervention group will receive an advanced CKD education module with information about CKD risk factors, stages, treatment options, and lifestyle modifications. The RA will assist in advancing program modules but not offer any information or knowledge about CKD. The avatar will be an African American woman who will present statistics about African American individuals and CKD. The interactive component will allow participants to personalize the information received based on prior CKD knowledge, diabetes status, and the level of motivation. The interactive CKD video can be completed in 30-45 minutes. Following the patient’s completion of the advanced CKD education module, the RA will then readminister the General Health Knowledge and Intent survey.

The computerized adaptive education intervention group (and the usual health care control group) will complete the “What’s Next” form, to assess the patient’s commitment to specific self-care activities. Patients will select 3 health goals from a list of 10 options, rate their level of confidence in the ability to make change, and identify an action plan to accomplish each goal. Moreover, patients will be asked to report their needs from the medical care team and for community assistance, and they will be provided a resource list. The study will also ask if patients would like a primary care doctor and/or a nephrologist. This information will be relayed to the primary inpatient team. All the forms will be sent to the patient educator, a trained nephrology social worker.

We will encourage participants to complete the voluntary study in one visit. At 30 days after discharge, both groups will complete a follow-up call with the project RA. Participants will be queried about progress on goals set on the health commitment form, knowledge, and health intent.

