### Outcomes

#### Primary Outcome

The primary outcome of this study is the changes in patient knowledge, attitudes, and behavior about CKD and RRT. To evaluate CKD and CKD self-care knowledge, we will use a modified Kidney Knowledge Survey; the CKD Self-Management Knowledge Toolkit, which is a validated instrument [8,9]; and an investigator-developed ESKD knowledge survey. We will measure the change from the baseline observed via the pretest, posttest, and follow-up surveys. The pretest and posttest surveys comprise 20 mixed format multiple-choice and Likert-scale questions (ranging from strongly agree to strongly disagree; from no knowledge to a great deal of knowledge; and from extremely unlikely to extremely likely) to examine the patient’s basic understanding of their health, general CKD knowledge, and health management.

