### Statistical Methods

The planned total sample size is 170 (85 per group), which accounts for participant dropout due to unexpected discharges, changes in clinical status, or study disenrollment. The primary outcome will be measured by the change in baseline observed via the pretest, posttest, and follow-up surveys. Using a 2-sample, 2-tailed *t* test, a total of 154 (77 per group) participants is required to obtain >90% power to detect at least a 10% difference with the most conservative SD of 21% with a 1-sided type-1 error of 5%.

Our team will use the paired, 2-tailed *t* test with a Bonferroni adjustment for multiple comparisons with the usual hospital care and computerized adaptive education groups. We will use one-way ANOVA and chi-square tests to examine the significance between the usual hospital care and computerized adaptive education groups. This will determine whether there is a statistically significant difference between the two groups. We will also determine if the difference between observed and expected data is because of chance or a relationship between the usual health care and computerized adaptive education groups.

Data analysis will take place in an UCMC office. We will continue to monitor patient medical records after the study to determine whether they may be later included or excluded from the study.

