## Results

Recruitment for the I-C-CKD study began May 2, 2023. We are currently recruiting and have enrolled 96 patients who completed both pretest and posttest surveys as of December 2024. This includes 50 patients in the control group and 46 patients in the intervention group. Data analysis has not occurred. We will communicate trial results to trial participants, health care professionals, and the public via a journal publication.

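### Participants who deteriorate in hospital are withdrawn from the whole study, not only the session, which conflicts with the promised 30-day contact and would forgo primary-outcome data

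*Protocol article*

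**What the plan says.** Ethical Considerations gives a general rule: "Discontinuation will also occur if patients are in acute distress or experience declining health conditions during hospitalization". Its example covers intensive care, intubation, or a patient who "has an altered mental status and can no longer participate, then we will withdraw them from the study". What the patient leaves is the study; the session and the education module are not mentioned separately.

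Statistical Methods treats such events as loss from the trial. It plans 170 participants, "which accounts for participant dropout due to unexpected discharges, changes in clinical status, or study disenrollment".

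Other sections say the opposite about follow-up. Intervention Group states: "At 30 days after discharge, both groups will complete a follow-up call with the project RA". Trial Design and Secondary Outcomes likewise have every patient contacted 30 days after discharge. None makes an exception for withdrawn participants.

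Two further statements decide why this matters. Under Randomization, the research assistant (RA) reads the allocation from the spreadsheet first, and then: "They will then approach the patient with the appropriate form and study packet". Under Primary Outcome: "We will measure the change from the baseline observed via the pretest, posttest, and follow-up surveys". Blinding adds that the research team knows the allocation.

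**The concern.** A rule that stops a bedside session when a patient becomes too ill is ordinary. A rule that ends study participation at the same moment does more: it removes someone already randomised because of something that happened after allocation. Acute distress and declining health call for judgement, and those judging know the group.

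Two things are at stake. First, a participant who recovers and goes home may well be able to answer a telephone survey 30 days later. If withdrawal from the study is followed literally, that call is not made, and part of the primary outcome and the 30-day secondary scales are forgone. No analysis plan can recover data that were never collected. Second, the participants who remain are a selected, less sick subset. If that selection differs between groups, the comparison is no longer purely the randomised one.

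**Working it through.** **1. Is the removal after randomisation?** Randomization allocates before the approach; Trial Design places allocation after verbal consent. On either order, worsening during or after the session follows allocation.

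**2. Does it touch the primary outcome?** Yes. Primary Outcome and Statistical Methods both include the follow-up survey in the measured change, and Intervention Group places follow-up at 30 days after discharge. Secondary Outcomes repeats its scales then too.

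**3. Do the sections agree?**
- Ethical Considerations: withdrawn from the study.
- Statistical Methods: change in clinical status is a form of dropout.
- Trial Design, Intervention Group, Secondary Outcomes: 30-day contact for each patient or both groups, no exception.

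The first two point to loss from the trial and the other three to continued follow-up. A research assistant could follow either.

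**4. The plan's own allowance.** Inputs from Statistical Methods: difference 10 points, SD 21, one-sided 5%, power above 90%.
- Normal approximation: n per group = 2 × (1.645 + 1.282)² × 21² / 10² = 75.6, rounded up to 76.
- Noncentral t: power is 0.899 at 76 and 0.903 at 77 per group. The stated 77 per group (154 in total) is reproduced.
- Allowance: 170 − 154 = 16, and 16/170 = 9.4%.

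This 9.4% covers every cause of loss. No rate is given for clinical worsening, overall or by group.

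**5. Possible shift in the group contrast.** Let w be the share withdrawn in a group, and g the amount by which withdrawn participants would have changed less than retained ones.
- Mean of all randomised = (1 − w) × m + w × (m − g) = m − w × g, where m is the mean of those retained.
- The retained mean therefore exceeds the full mean by w × g.
- With the same g in both groups, the contrast shifts by g × (w₁ − w₀), where 1 is intervention and 0 is control.

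The documents give neither w nor g, so these inputs are assumptions:

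| Difference in withdrawn share | g | Shift |
|---|---|---|
| 0 | 10 points | 0 |
| 5 percentage points | 10 points | 10 × 0.05 = 0.5 point |
| 10 percentage points | 10 points | 10 × 0.10 = 1.0 point |

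The sign follows whichever group loses more, and reverses if g is negative. If g differs between groups, the shift is w₁g₁ − w₀g₀, so equal shares alone do not guarantee zero.

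**The case against.** The strongest reply is that the article never says withdrawn patients are not called, and three sections promise the contact to everyone. That stands: the loss of the 30-day outcome is the consequence of following Ethical Considerations literally, not a stated fact. It leaves a contradiction that has to be resolved.

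A second reply is that the example is limited to patients who can no longer participate, and that the broader sentence before it does not define discontinuation. This also stands in part. Participants are encouraged to finish in one visit, so application of the rule to someone who has already completed the posttest is an inference. But inability to take part in hospital is not inability 30 days after discharge.

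A third is that analysis populations and the handling of withdrawn participants' data belong to a fuller protocol or analysis plan. That is right. A reader might infer that collected pretest and posttest data are deleted, but nothing says so. The point here is the stated rule and the data it would leave uncollected.

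The parent Hospitalist Project has its own 30-day telephone follow-up, but nothing says that it collects this trial's outcomes.

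Further readings go beyond the documents:
- **Longer exposure in the intervention group.** Intervention Group says: "The interactive CKD video can be completed in 30-45 minutes". A reader might infer that this group has more time in which to be withdrawn before its posttest. Control Group, however, also mentions a video module before the control posttest, so a shorter control session cannot be assumed.
- **Exclusion already happening.** Results reports that the investigators "have enrolled 96 patients who completed both pretest and posttest surveys as of December 2024". This is a progress count and does not show removal under this rule.
- **Recovered power.** Comparing 77 with 85 per group would assume that every loss from every cause is recovered. This change would recover only some 30-day calls and no missing posttests.

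**Conclusion.** The point holds as a contradiction between sections and as a withdrawal rule that reaches too far. Taken as written, Ethical Considerations removes randomised participants after allocation, by an unblinded team, and forgoes 30-day primary-outcome data from those who recover and could answer.

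The documents do not establish the size or direction of any bias. It is near zero if the share and type of patient withdrawn are the same in both groups. Under the assumptions in the table it is about 0.5 to 1 point, or 5% to 10% of the 10-point target. The likely effect is modest. The case for change rests on keeping the randomised comparison intact at little cost, not on a demonstrated distortion.

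**What to change.** Leave the clinical triggers and the stopping of the session unchanged. Reconcile Ethical Considerations, Statistical Methods, Trial Design, Intervention Group and Secondary Outcomes so that they distinguish stopping the in-hospital session from withdrawal from the study. State that:

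- a participant whose session is stopped stays in the allocated group, with the data already collected kept;
- the 30-day call is attempted unless consent has been withdrawn or the participant still cannot participate;
- the number of stopped sessions and the reasons are reported by group.

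The cost is a protocol modification reported to the institutional review board (IRB), with whom continued participation after a temporary loss of capacity should be settled, since the protocol excludes patients who need a proxy for consent. There will be a few extra calls by the RA who already makes them. Some calls will fail, leaving missing values to be handled in the analysis. Recruitment was still open and no analysis had been done as of December 2024, so at that date the change could still have helped later participants.

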## Results

Recruitment for the I-C-CKD study began May 2, 2023. We are currently recruiting and have enrolled 96 patients who completed both pretest and posttest surveys as of December 2024. This includes 50 patients in the control group and 46 patients in the intervention group. Data analysis has not occurred. We will communicate trial results to trial participants, health care professionals, and the public via a journal publication.

## Discussion

We believe our study will result in the computerized adaptive education intervention group experiencing a greater improvement in CKD knowledge, CKD health-seeking behavior, and self-care in comparison to the control group. The goal of this study is to increase hospitalized African American patients’ knowledge of CKD and motivation for CKD self-care. We have created and will assess a culturally tailored, computerized adaptive education intervention that expands on the information gathered from in-person interventions. Computerized adaptive education can evaluate patients’ concerns and provide personalized education. Customized patient education information is more likely to be recalled and significantly influence a patient’s motivation and behavior modification.

African American patients diagnosed with CKD experience inequities in the quality of health education, self-care, and medical treatment for ESKD [13]. Patient education can encourage African American patients with advanced-stage CKD to make informed decisions and take control of self-care and health decisions to delay progression to ESKD. Providing CKD education during hospitalization can address gaps in care to help patients initiate preventative care, plan for future RRT, and build a treatment team that aligns with their health and lifestyle preferences.

This intervention focuses on hospitalized African American patients who represent more than 80% of the general medicine population at our medical center. The intervention is culturally tailored to African American patients. The hospital also serves patients who are not followed by routine medical providers and have trouble accessing outpatient care due to limited transportation, limited or no insurance, mobility issues, and socioeconomic constraints [14]. Hospitalized patients may be more open and responsive to CKD education efforts when they are focused on their health during a hospital stay. The intervention can also link these patients to outpatient care. We will also ask if patients would like a primary care doctor and/or a nephrologist. This information will be relayed to the primary inpatient team.

Limitations of this study include the single-hospital study design, which reduces the generalizability of the results. In addition, we are testing the intervention only among hospitalized African American patients who are generally admitted with urgent or acute health concerns, which may reduce their ability to fully participate or complete this study. An additional barrier for inpatient kidney education to be disseminated on a large scale is that the results may differ among a different group or in a different health care setting.

In conclusion, African American individuals often receive less patient education about self-care and medical treatments for CKD. We hope our study provides one way to reduce this disparity. However, to improve CKD outcomes, African American patients—and all patients with CKD—require frequent, understandable education about CKD across all sites of care.

## Appendix

Multimedia Appendix 1 Institutional review board–approved consent form.

Multimedia Appendix 2 SPIRIT (Standard Protocol Items: Recommendations for Interventional Trials) checklist.

## Abbreviations

CKD: chronic kidney disease
eGFR: estimated glomerular filtration rate
ESKD: end-stage kidney disease
I-C-CKD: Interactive Computer-Adaptive Chronic Kidney Disease
IHD: in-center hemodialysis
IRB: institutional review board
PREP RRT: Patient Referral and Education Program Prior to Renal Replacement Therapy
RA: research assistant
RRT: renal replacement therapy
SPIRIT: Standard Protocol Items: Recommendations for Interventional Trials
UCMC: University of Chicago Medical Center
